### Recruitment

Based on data from our registry, if we assume 40% of patients will present with moderate to severe psychological distress and exclude patients who have a poor command of English (10%), 450 patients would be eligible for inclusion over a 20-month recruitment period. Presuming a conservative recruitment rate of 1 in 3, target recruitment is achievable within the study timeframe. Potential participants will receive both verbal and written information about the requirements of participation including i) verbal explanation of the program content upon initial contact and ii) detailed outline of the program content and required commitment in the patient information and consent form. Consistent with our existing recruitment strategy for randomised controlled trials, patients will receive i) written material for study participants and ii) travel assistance and telephone reminders of scheduled appointments; strategies proven to improve recruitment and retention rates in interventional studies [45]. Of importance and to avoid bias, these strategies will be employed with patients in both study arms.

### Randomisation and masking

Following consent, block randomisation will be used to determine which participant receives the intervention according to a computer-generated random assignment sequence prepared in advance. Considerable effort will be made to avoid observer bias through separation of roles and blinding of trial staff. A research assistant independent of patient recruitment and data collection will be responsible for co-ordination of patient appointments, telephone reminders, and travel assistance. The research associate (who will be responsible for patient consent) will be blinded to group allocation. Mindfulness training will be conducted by investigators who will remain blinded to outcome data throughout the study. Upon completion of the study, a biostatistician blinded to group allocation will analyse outcome data.

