**Methods/Design:**

One hundred and fifty people with end-stage arthritis on the waiting list for total hip or knee arthroplasty will be recruited and randomly allocated to one of two groups using computer-generated block randomisation. A randomised controlled trial adhering to CONSORT guidelines will evaluate the efficacy of a mindfulness training program (weekly group-based classes in mindfulness practice, 2 ½ hours, for 8 weeks plus a 7-hour Saturday session in Week 6) prior to total joint arthroplasty, compared to a “standard care” group who will undergo routine total joint arthroplasty. Primary outcomes will be evaluated by a blinded examiner at baseline, 3 and 12 months post-surgery, using a validated self-reported pain and physical function scale. Secondary outcomes will include i) a range of validated measures of psychological wellbeing and ii) health economic analysis. All analyses will be conducted on an intention to treat basis using linear regression models. Health economic modelling will be applied to estimate the potential cost-effectiveness of mindfulness training and total joint arthroplasty.

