## Background

Osteoarthritis is a leading cause of disability in developed nations. In Australia, it afflicts 16.5% of the adult population and imposes a significant economic burden [1]. Total joint arthroplasty (TJA) is considered the treatment of choice for end-stage osteoarthritis. However, the success of TJA, a high volume, expensive procedure, is undermined by pre-operative psychological distress, a known predictor of suboptimal improvement after surgery. Psychological co-morbidities and traits reported in TJA patients include depression, anxiety, neuroticism, catastrophizing, poor self-esteem, and low self-efficacy, all of which are associated with poorer function and greater pain after TJA in short and longer term follow-up studies [2-7].

Our recent comprehensive literature review found pre-operative psychological distress to be an independent predictor of pain and function after TJA in a majority of published studies [8]. This relationship has also been noted for other major surgical procedures, e.g., herniated disc surgery [9] and coronary artery bypass graft surgery [10]. In a large prospective study involving more than 1,000 TJA recipients, we showed that poorer pre-operative mental health scores were associated with weight gain after surgery [11]. Obesity is over-represented in TJA candidates (hip patients > 40% obese, knee > 60%) and only 10% show clinically significant weight loss after surgery [11,12]; obesity itself is strongly associated with depression [13]. Pre-operative psychological distress is also associated with excessive analgesic intake, higher rates of hospital readmission, and long-erm mortality [14].

Despite such findings, there is a dearth of literature examining psychological interventions or programs in surgical patients generally, and, to the best of our knowledge, there are no published intervention studies specifically for TJA. Thus, there is a pressing need to examine whether implementing a mental health enhancement program improves postoperative outcomes in patients undergoing TJA, a question with relevance to other surgical programs and to the health of the aged more generally.

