### Outcome assessments

#### Data capture

Outcomes will be captured by the research associate. Demographic information collected at baseline will include age, gender, co-morbidities, body mass index, and socioeconomic data. We will also collect ‘time’ on the waiting list. All MT sessions will be audio-taped and a random sample will be selected and assessed for adherence to the principles of MT. Fully-itemised costs of healthcare will be captured via SVHM’s hospital network, including administered medications as well as costs of hospital in-patient and out-patient encounters. While beyond the scope of the initial Discovery Project time frame, the investigators will include a longer term follow-up plan in the ethics application to allow scope for continued data capture in the study group at the annual outpatient review to 10 years.

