### Sample size

The sample size calculation was based on the following parameters: i) alpha value = 0.05, 2-sided; ii) power = 80%; iii) expected rates of the primary outcome 1-year post-TJA. To determine the sample size, we reviewed the data from our SVHM joint registry from 2009 to 2010 [44]. Of 1,180 patients who underwent TJA, 40% showed moderate to severe pre-operative psychological distress according to the pre-operative SF-12 MCS score. The mean difference in functional outcome scores at 12 months post-TJA between individuals with moderate to severe pre-operative psychological distress and individuals with no or mild psychological distress was 10 (+20) points. Based on these data, the sample size required in each of the 2 groups is 64. To allow for 15% attrition, 150 patients will be recruited in total. These numbers will also give more than 80% power to detect the expected minimum clinically important difference in pain and functional outcome scores between the combined MT + TJA group and the TJA alone group.

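### Hip and knee patients are pooled, yet the stated primary comparison of WOMAC leaves joint out; making it a prespecified covariate is a small, nearly free gain

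*Protocol article*

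**What the plan says.** - **Population.** The abstract states that "One hundred and fifty people with end-stage arthritis on the waiting list for total hip or knee arthroplasty will be recruited". The inclusion criteria ask only for primary total joint arthroplasty, so both joints enter one comparison.
- **Allocation.** The abstract has patients "randomly allocated to one of two groups using computer-generated block randomisation". Randomisation and masking says that "block randomisation will be used to determine which participant receives the intervention according to a computer-generated random assignment sequence prepared in advance". Neither place names a stratification factor.
- **Difference between the joints.** The Background reports different obesity rates: "hip patients > 40% obese, knee > 60" per cent. No section gives WOMAC scores by joint.
- **Baseline data.** Data capture says "Demographic information collected at baseline will include age, gender, co-morbidities, body mass index, and socioeconomic data". Index joint is not in that sentence.
- **Analysis.** The Statistical analysis section assigns continuous outcomes to t-tests or Mann-Whitney tests according to the shape of the distribution. Adjustment for baseline variables is a secondary analysis, used if chance imbalance appears. The abstract says that all analyses are by linear regression.
- **Planning figures.** Sample size uses "alpha value = 0.05, 2-sided", 80% power and a 12-month difference that "was 10 (+20) points", taken from a registry of 1,180 arthroplasty patients not split by joint. It arrives at 64 per group and 150 in total.

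**The concern.** Blocking without strata keeps the arm totals close. It does not keep the share of hips and knees equal between arms. If the two operations lead to different WOMAC scores at 12 months, two things follow under an unadjusted test. A chance excess of one joint in one arm moves the estimated effect, and the variation between joints stays in the error term in every case.

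Joint is known before randomisation, so both can be dealt with in advance. The Methods leave adjustment until imbalance has been looked for, and then only as a secondary result. At stake are a little precision and a clear statement, before the data are seen, of which analysis is primary.

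**Working it through.** **1. The plan's own figure.** Read the bracketed 20 as the SD.
- Normal approximation: n per arm = 2(1.960 + 0.842)² × 20² / 10² = 62.8, so 63. The t-based calculation gives 63.77, so 64, as stated.
- Attrition: 128 / 0.85 = 150.6, so 151, against 150 stated; 150 × 0.85 = 127.5. The stated figures reproduce within rounding.
- Power at 64 per arm is 80.7% (normal) or 80.1% (t-based).

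**2. How far the joint mix can drift.** The documents do not give the mix, so a knee share p of 30% to 50% is assumed. The SD of the between-arm difference in share is √(2p(1−p)/n).

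| Patients per arm | SD (points) | 95% range (points) |
|---|---|---|
| 75 (randomised) | 7.5 to 8.2 | ±15 to ±16 |
| 64 (analysed) | 8.1 to 8.8 | ±16 to ±17 |

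At 75 per arm, a difference of 10 points or more has probability 18% to 22%.

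**3. What that does to the estimate and to power.** Let g be the hip-knee difference in mean 12-month WOMAC. The documents give no value, so g = 5 and g = 10 are assumed, with p = 50% and 64 per arm.
- Shift at the 95% limit of imbalance = 1.96 × g × √(2 × 0.25/64).
- Share of variance due to joint = 0.25g²/400.
- Residual SD = 20√(1 − share).
- Power is recalculated with that SD (normal approximation).

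| g | Shift (points) | Variance share | Residual SD | Power, joint removed | Gain over 80.74% |
|---|---|---|---|---|---|
| 5 | 0.87 | 1.6% | 19.84 | 81.35% | 0.6 points |
| 10 | 1.73 | 6.25% | 19.36 | 83.18% | 2.4 points |

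The shift is not an extra error on top of the standard error. The unadjusted standard error, 20√(2/64) = 3.5 points, already contains it.

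**4. Stratification or adjustment?** The trial was simulated with 128 patients, blocks of 4, g = 10, p = 50% and 8,000 runs per case.

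| Allocation | Analysis | Power | Type I error |
|---|---|---|---|
| Not stratified | Unadjusted | 80.0% | 5.0% |
| Not stratified | Adjusted for joint | 82.4% | 4.9% |
| Stratified | Unadjusted | 80.9% | 3.8% |
| Stratified | Adjusted for joint | 82.8% | 4.8% |

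The Monte Carlo standard error of each power figure is about √(0.8 × 0.2/8000) = 0.45 points. The 0.4-point difference between the two adjusted rows is therefore within simulation noise, as are the differences in the matching runs at g = 5. Almost all of the gain at g = 10 comes from having joint in the model. The third row shows that if the lists are in fact stratified, leaving joint out of the analysis makes the test conservative. Either way, joint belongs in the model.

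**The case against.** The strongest case against is that simple block randomisation of 150 patients is valid and that nothing here is an error. Much of that stands.

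- *A reader might infer that the trial uses a single list that ignores joint.* The article does not say so. It names no stratification factor in either description, but it condenses a fuller protocol that is not shown.
- *A reader might infer bias or a false-positive problem.* The simulation does not support this: type I error stays near 5% without stratification.
- *A reader might infer that 64 per group is too few.* The SD of 20 appears to come from a registry of all arthroplasty patients. If so, it already contains the variation between joints, and the stated power holds.
- *A reader might infer that joint goes unrecorded.* The Data capture sentence concerns demographic information and is not worded as a complete list. The planned operation is known from the waiting list.
- *The obesity figures show that the two groups differ.* They are not WOMAC figures. If g is zero, nothing is lost.

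It is also fair to say that linear regression, as named in the abstract, could carry joint as a covariate. That does not remove the point. The abstract names no covariate, and the Methods describe unadjusted tests with adjustment conditional and secondary. The two statements of the analysis do not agree.

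**Conclusion.** The point stands as a minor improvement to the analysis. It is not a flaw in validity or sample size. As the Methods are written, a probable prognostic factor known before randomisation is left out of the primary comparison, and whether an adjusted result appears at all depends on an imbalance seen in the data.

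The power forgone is about 0.6 points if the joints differ by 5 points at 12 months and about 2.4 points if they differ by 10. This rests on an assumed equal mix of hips and knees, an assumed difference, 64 analysed per arm, and reading the planning figure of 20 as an SD. The numerical gain is modest. The clearer benefit is that one adjusted analysis is fixed in advance and the abstract and Methods are brought into line.

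**What to change.** In the Statistical analysis section, make the primary analysis of WOMAC pain and of WOMAC function at 12 months the linear regression already named in the abstract, with index joint (hip or knee) as a prespecified fixed covariate for all patients. Replace the wording that makes adjustment depend on observed imbalance. In Randomisation and masking, add one sentence saying whether the sequence is stratified by joint.

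Stratifying the block sequence is optional. The trial is open to recruitment, so changing the lists now would leave a mixed allocation scheme for a gain of about 0.4 points in the simulation, which is within its noise.

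The cost is one model term, one degree of freedom and a recorded field for the joint operated on. No extra patients, visits or staff are needed.

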### Data management

All data is stored on a password protected computer kept in a secure locked facility and only accessible to the Chief Investigators and Trial’s Coordinator as approved by the SVHM Human Research Ethics Committee. At the completion of the study, outcome data will be pooled and de-identified for analysis by a statistician.

### Statistical analysis

Statistical analysis will be by intention to treat. Categorical variables will be analysed using χ^2^ tests (or Fisher’s Exact test for small samples) while for continuous variables we will employ (parametric) *t*-tests and (non-parametric) Mann-Whitney tests for symmetrically and asymmetrically distributed data, respectively. The significance of differences in dichotomous data will be tested using generalised estimating equations or linear mixed model. If there are chance imbalances in baseline patient characteristics hypothesised to influence the main outcomes, then statistical techniques that allow adjustment for confounding variables will be used as secondary analyses. If there are more than 5% missing data, sensitivity analyses allowing for different assumptions, such as the best or worst possible scenario, will also be reported for the main outcomes of the study.

Health economic modelling will be applied to estimate the potential cost-effectiveness of MT + TJA. Decision analysis [46] will be used to compare the downstream consequences of MT + TJA versus TJA alone. The incorporation of Markov [47] and life-tabling [48] techniques will allow for the modelling of outcomes beyond one year. The main output of interest in health economic modelling is incremental cost-effectiveness ratios in terms of net costs per unit of health gain. Net costs will comprise the costs of MT + TJA minus costs saved from the reduction in downstream health services utilization. Health gains will be measured by estimating years of life gained and quality-adjusted life years gained. Both are enabled by the collection of time-to-outcome data and the latter also by collection of QoL data. All health economic analyses will be undertaken in accordance with recommended approaches, such as 5% discounting of estimated future costs and health gains. To account for any uncertainty in the data inputs for health economic modelling, sensitivity and uncertainty analyses will be undertaken via Monte Carlo simulation [49].

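### The Methods leave the WOMAC effect measure to the shape of the data and keep baseline WOMAC out of the primary comparison, and the abstract states a different analysis

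*Protocol article*

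**What the plan says.** The Primary outcome section names two WOMAC subscales, pain and physical function, each scaled 0 to 100. The abstract has them measured at baseline, 3 and 12 months, and the Experimental design section compares the arms at 12 months.

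Four statements bear on how they are analysed:

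- **Test for continuous variables** (Statistical analysis): t-tests and "non-parametric) Mann-Whitney tests for symmetrically and asymmetrically distributed data, respectively". No criterion for symmetry is given.
- **Adjustment** (same section): "If there are chance imbalances in baseline patient characteristics hypothesised to influence the main outcomes", adjusted methods are then used, as secondary analyses. No covariate is named.
- **Model-based methods** (same section): "The significance of differences in dichotomous data will be tested using generalised estimating equations or linear mixed model".
- **Abstract, Methods/Design**: "All analyses will be conducted on an intention to treat basis using linear regression models".

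The Sample size section plans on a difference and spread given as "no or mild psychological distress was 10 (+20) points", with "alpha value = 0.05, 2-sided" and 80% power. It concludes that "the sample size required in each of the 2 groups is 64".

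**The concern.** Three things are unsettled for the main outcome.

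1. **Effect measure.** A t-test estimates a difference in mean WOMAC points. A Mann-Whitney test compares ranks. Choosing between them by the shape of the observed scores means that the quantity reported is not known until the data are seen. If the rank test is used, nothing in the main result can be read against the 10 points used for sizing.
2. **Use of baseline.** In a randomised trial the main reason to adjust for a prognostic baseline value is precision, and that reason holds whether or not the arms look imbalanced. Here imbalance is the trigger, and even then the adjusted result is only secondary.
3. **Conflict over the method.** The abstract names linear regression for everything, and the Statistical analysis section never mentions it. The only methods there that suit repeated measurements are attached to dichotomous data, although the WOMAC scores are continuous and repeated.

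At stake are a primary result whose form is open, precision given up at no saving, and a public record from which a reader cannot tell which analysis was planned.

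**Working it through.** **Inputs from the Sample size section.** Two-sided alpha 0.05, power 80%, difference 10 points, SD 20 (reading the plus sign in the text as plus-or-minus), 64 per group, and "To allow for 15% attrition, 150 patients will be recruited in total". **Assumed:** the correlation r between baseline and 12-month WOMAC, taken as 0.2 to 0.6.

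**Step 1: reproduce the plan's figure.**
- Normal approximation: n = 2(1.96 + 0.8416)² × 20² / 10² = 62.8, so 63 per group.
- Noncentral t: 63.8, so 64 per group, as stated. Power at 64 is 80.1%.
- Attrition: 128 / 0.85 = 150.6, against the stated 150.

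The SD reading is confirmed, and the sample size matches an unadjusted two-sample test.

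**Step 2: adjust for baseline.** The residual SD is 20 × √(1 − r²). Power uses the same t calculation at 64 per group. The 95% half-width is 1.96 × 20 × √(2/64) × √(1 − r²), and the first part of that product is 6.93.

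| r (assumed) | Residual SD | Power | Half-width (points) | n per group for 80% |
|---|---|---|---|---|
| unadjusted | 20.0 | 80.1% | 6.9 | 64 |
| 0.2 | 19.6 | 81.7% | 6.8 | 62 |
| 0.3 | 19.1 | 83.7% | 6.6 | 59 |
| 0.4 | 18.3 | 86.5% | 6.4 | 54 |
| 0.5 | 17.3 | 90.0% | 6.0 | 49 |
| 0.6 | 16.0 | 93.9% | 5.5 | 42 |

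(With the t quantile in place of 1.96 the unadjusted half-width is 7.0.)

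**Step 3: cost of the rank test.** For normal data its asymptotic efficiency is 0.955, an effective 64 × 0.955 = 61.1 per group. Power by the normal approximation is then 78.9%, against 80.7% for the t-test on the same approximation. The loss of power is small. The change in what is estimated is the real issue.

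**Step 4: does choosing the test from the data inflate type I error?** The article gives no rule, so a Shapiro-Wilk pre-test in each arm stood in for it. In 8,000 simulated null trials of 64 per group, the two-stage procedure rejected in 4.6% with normal data and 4.9% with skewed (gamma) data. No inflation was seen.

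**Step 5: set the two method statements side by side.** A t-test is a linear regression with one binary covariate, so that half of the Methods rule fits the abstract. Mann-Whitney, chi-square and Fisher tests are not linear regressions, so the abstract's claim about all analyses cannot hold together with the Methods.

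**The case against.** **The sample size is sound.** The trial was sized for an unadjusted test, and that sizing reproduces. Adjustment would add power above the target and repair no shortfall. This stands. The size of the gain also depends wholly on a correlation that the article does not give. Surgery falls between the two measurements, so a low value is possible, and at r = 0.2 the gain is only 81.7 − 80.1 = 1.6 percentage points.

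**The rules are generic.** The section does not name WOMAC, nor say whether a t-test would use the 12-month score or the change from baseline. A change score would use baseline. This stands in part. With equal SDs at both times, the SD of change is 20 × √(2(1 − r)): 25.3 at r = 0.2, 20.0 at r = 0.5 and 17.9 at r = 0.6. It is never below the regression's 20 × √(1 − r²), because 1 + r cannot exceed 2. The abstract's regression could also include baseline, but nothing says that it does.

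**Imbalance gives a choice of primary result.** A reader might infer that the imbalance trigger lets the investigators pick between two headline results. The text does not support this: adjusted analyses are labelled secondary, so the hierarchy is fixed. Imbalance decides only whether an adjusted result exists.

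**False positives.** A reader might also infer an inflated error rate from switching tests. The simulation does not show one.

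**Linear mixed model for binary data.** To call it simply wrong goes too far, since a linear model for a binary outcome can estimate a risk difference. What remains is that the sentence gives the repeated-measures methods to dichotomous data and not to the repeated continuous scores.

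**Condensed article.** A fuller plan may name a model. That would not remove the disagreement between abstract and Methods, or the stated trigger for adjustment.

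**Conclusion.** The point holds as a matter of specification and precision. On the text, the effect measure for the primary outcome depends on the observed distribution, the primary comparison makes no use of baseline WOMAC as a covariate, and the abstract and Methods cannot both be right.

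The size is an unclaimed gain: from 80.1% power to between 81.7% and 93.9% at 64 per group for r between 0.2 and 0.6, with the 95% half-width falling from 6.9 to between 6.8 and 5.5 points. These figures assume SD 20, a 10-point difference and the stated range of r. They do not show that the sample size is wrong or the trial underpowered. The contradiction and the open effect measure rest on no assumption about r. The change should be made, but the trial's validity does not depend on it.

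**What to change.** In both the abstract and the Methods, name one primary model for each WOMAC subscale: a linear regression of the 12-month score on arm and the baseline value of the same subscale, with joint (hip or knee) as an optional covariate. Use it whatever the imbalance or distribution.

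- Deal with skewness by robust or bootstrap standard errors, and keep Mann-Whitney as a sensitivity analysis.
- Remove the imbalance trigger.
- Use logistic GEE or a generalised linear mixed model for any dichotomous outcome.
- A linear mixed model on the 3- and 12-month scores is a reasonable alternative. It is not equivalent, because with attrition (15% is planned for) the two can give different answers. Choose one in advance.
- Confirm that baseline WOMAC is completed before randomisation, or at least before allocation is known. Table 1 places randomisation at Visit 1 and the baseline assessments at Visit 2, and a self-reported baseline given after learning the allocation is not a safe covariate.

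The cost is some rewording and a little analysis work. No new data or patients are needed. The one dependence is a valid baseline.

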#### Primary outcome

Will be self-reported pain and physical function measured on the Western Ontario and McMaster Universities (WOMAC) Osteoarthritis Index [32]. The WOMAC consists of 24 items covering three subscales: pain (five items), stiffness (two items), and physical function (17 items). The pain and physical function subscales will be used, each subscale transformed to a score ranging from 0 to 100, with a higher score indicating greater pain and physical function. The WOMAC is a widely-used questionnaire specifically designed to evaluate knee and hip osteoarthritis [33,34].

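### The repeated-measures models are assigned to dichotomous data, which already have another test and which no endpoint uses, while the continuous WOMAC scores get only single-time tests

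*Protocol article*

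**What the plan says.** All places are in the protocol article.

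- **Primary outcome:** the WOMAC pain and physical function subscales, "each subscale transformed to a score ranging from 0 to 100". No cut-point or responder definition is given. None of the secondary outcomes is defined as yes/no either.
- **Timing:** the Abstract and Table 1 (Timelines) place WOMAC at baseline, 3 and 12 months. Experimental design sets the comparison of the arms at 12 months.
- **Statistical analysis, first rule:** "Categorical variables will be analysed using χ"-square tests, or Fisher's exact test in small samples. Continuous variables get t-tests or Mann-Whitney tests, depending on symmetry.
- **Statistical analysis, second rule:** "The significance of differences in dichotomous data will be tested using generalised estimating equations or linear mixed model".
- **Abstract, Methods/Design:** linear regression is named for every analysis.
- **Sample size:** the listed inputs include "alpha value = 0.05, 2-sided" and "expected rates of the primary outcome 1-year post-TJA". No rate follows. The calculation uses a mean difference between distressed patients and "individuals with no or mild psychological distress was 10 (+20) points", and concludes that "the sample size required in each of the 2 groups is 64".

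**The concern.** A dichotomous variable is a categorical variable with two levels, so the two rules overlap completely, and nothing says when each applies. The second rule also offers a linear mixed model, which assumes a continuous response with normally distributed errors. For a yes/no response the usual choice is a model with a logit link. GEE can provide that, but a linear mixed model does not.

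The larger cost falls on the primary outcome. Generalised estimating equations and mixed models are the tools for repeated measurements, and the trial's repeated measurements are continuous scores. As written, those scores receive only tests that compare two groups at one time. The Abstract's linear regression is a further method for the same outcome. At stake is which analysis gives the primary result, and whether a patient with a 3-month score but no 12-month score contributes to it.

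**Working it through.** **Step 1. Does the sample size treat the primary outcome as a score?**

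Inputs from Sample size: two-sided alpha 0.05, power 80%, difference 10 points, and +20 read as an SD of 20 (an assumption; a plus-minus sign was probably lost). Equal allocation is inferred from the equal group sizes.

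- Standardised difference: d = 10/20 = 0.5.
- Normal approximation: n = 2(1.960 + 0.842)²/0.5² = 2 × 7.85/0.25 = 62.8, so 63 per group.
- Two-sample t-test: n = 63.77, so 64 per group, which is the stated figure. Power at 64 per group is 80.1%.
- Attrition ("To allow for 15% attrition, 150 patients will be recruited in total"): 128/0.85 = 150.6, against the stated 150. This agrees within rounding.

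The figure reproduces as a comparison of two means. That supports the SD reading and shows that no proportion entered the calculation. The word rates is a wrong label for an input that is a mean difference and an SD.

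**Step 2. Which rule reaches which data?**

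| Data | Used by a defined endpoint? | Methods named |
|---|---|---|
| Dichotomous | No | Chi-square or Fisher (as categorical); GEE or linear mixed model; linear regression (Abstract) |
| Continuous, including WOMAC at 3 and 12 months | Yes, the primary outcome | t-test or Mann-Whitney; linear regression (Abstract) |

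The only methods in the list built for repeated measurements sit in the row that no endpoint uses. A linear mixed model suits the second row and not the first.

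**Step 3. What does the misplacement change for the primary result?**

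A t-test or Mann-Whitney test at 12 months uses only patients with a 12-month score. The plan expects 15% attrition: 0.15 × 150 = 22.5, or about 22 patients. Those among them who have a 3-month score drop out of a 12-month test but contribute to a mixed model fitted to both visits, under the usual missing-at-random assumption. The article does not say how many that would be. If all scores were present, a mixed model with a treatment-by-visit term, an unstructured covariance and no further covariates would give the same 12-month mean difference as the t-test. The change therefore does not alter the quantity for which the trial was sized.

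**The case against.** **The two rules may have been meant for different uses.** Chi-square and Fisher could be for single-time comparisons such as baseline characteristics, and GEE for outcomes repeated over visits. This is a sensible reading, and the word dichotomous may even be a slip for longitudinal. But the section says neither, and guessing the intended word does not repair the rule.

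**No defined endpoint is dichotomous, so the faulty sentence decides nothing.** This stands as far as dichotomous data go, and it limits the weight of the contradiction. It does not cover the other half: by placing the repeated-measures models there, the text leaves the repeated WOMAC scores without one.

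**Preferring a mixed model to a 12-month t-test or regression is a matter of taste, and model details belong in an SAP.** In part this stands. A single pre-stated 12-month regression would also be a valid primary analysis, and covariance structure and covariates can be left to the SAP. But the article does state methods here, and they disagree with each other. The mixed model is one the plan already names, and it retains patients seen only at 3 months.

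**A stronger reading.** From the word rates in Sample size and the sentence on dichotomous data, a reader might infer that WOMAC will be cut into responders and that the trial then falls short of 80% power. The documents do not support this. WOMAC is defined as a score, the calculation uses a mean difference, the Abstract names linear regression, and no cut-point or responder rate appears anywhere. Any power figure for a dichotomised primary would rest on an invented cut-point. Likewise, a power comparison between chi-square at 12 months and a model pooled over visits depends on what is assumed about the effect at 3 months, and its direction reverses with that assumption.

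**Conclusion.** The point holds as a defect of the analysis text. Dichotomous data have two conflicting rules, one of which includes a model for continuous responses. The repeated-measures models are attached to a data type that no endpoint uses. The primary WOMAC scores are left with t-tests or Mann-Whitney tests in one place and linear regression in another.

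Its size is not a loss of power. The stated 80% with 64 per group is correct for the continuous score (80.1%), provided that +20 is an SD of 20. The practical consequence is that the primary analysis is not fixed to one method, and that a 12-month-only test discards the 3-month scores of some of the roughly 22 patients expected to be lost. The label rates in Sample size is a minor wording error.

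**What to change.** 1. **Statistical analysis, continuous scores.** Assign the linear mixed model to the WOMAC scores at 3 and 12 months, with a treatment-by-visit term, and name the 12-month contrast as the primary result, in line with Experimental design. State that this replaces the t-test/Mann-Whitney rule for the repeated scores.
2. **Abstract.** Reconcile the statement on linear regression with item 1, so that one method is named for the primary outcome.
3. **Statistical analysis, dichotomous data.** Keep one rule for any dichotomous outcome: either chi-square or Fisher's exact test at 12 months, or GEE with a logit link and the 12-month contrast reported. Remove the linear mixed model from that sentence.
4. **Sample size.** Replace the reference to rates with the expected mean difference and SD in WOMAC score.

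The cost is a few sentences, to be changed before unblinding. No extra patients, visits or data are needed, and the sample size stays as it is.
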